## Introduction

1

Intrahepatic cholestasis of pregnancy (ICP) is the most common hepatobiliary disorder unique to pregnancy, with a reported incidence of 2.9%, depending on geographic and ethnic factors (1). ICP is characterized by maternal pruritus and elevated serum bile acid concentrations, typically emerging during the third trimester. Although maternal symptoms resolve postpartum, ICP is associated with significant perinatal complications, including spontaneous preterm birth, meconium-stained amniotic fluid, fetal distress, and an increased risk of intrauterine demise (2, 3).

Beyond its established association with stillbirth and prematurity, emerging evidence has highlighted a potential link between ICP and neonatal respiratory morbidity. Several studies have demonstrated an increased incidence of RDS among neonates born to mothers with intrahepatic cholestasis of pregnancy, independent of gestational age at delivery (4, 5). Experimental data suggest that elevated fetal bile acid levels may interfere with surfactant synthesis or function, disrupt alveolar integrity and contribute to early pulmonary injury (6). However, the biological pathways underlying this relationship remain poorly understood.

Serum biomarkers of surfactant dysfunction and lung injury have been well characterized in the context of neonatal respiratory complications such as RDS and bronchopulmonary dysplasia (7). Nevertheless, no study to date has systematically evaluated these biomarkers in neonates exposed to maternal cholestasis. Consequently, it remains unknown whether intrauterine exposure to elevated bile acid levels induces biochemical evidence of surfactant impairment or pulmonary injury detectable at birth. Quantifying the extent of lung compromise in this population may not only provide insights into disease pathophysiology, but also support early risk assessment and targeted interventions in the neonatal period.

The CHOLE-RESP study has been designed to address these gaps by prospectively evaluating the incidence of RDS and the need for surfactant therapy in neonates born to mothers with ICP compared to matched controls. In addition, this study seeks to determine whether neonates exposed to intrahepatic cholestasis of pregnancy exhibit distinct serum biomarker profiles consistent with lung injury and surfactant impairment, thereby elucidating a potential link between maternal cholestasis and early neonatal respiratory dysfunction.

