### Eligibility criteria

2.4

Participants will be enrolled into either the exposed or unexposed group based on predefined eligibility criteria. The exposed group will consist of neonates born to mothers with a recent diagnosis of intrahepatic cholestasis of pregnancy, defined by serum bile acid concentrations exceeding 10 µmol/L within seven days prior to delivery. Furthermore, written informed consent needs to be obtained at least one hour prior to birth. No minimum gestational age at delivery is imposed and eligible neonates must be either born at the study location or transferred to the unit from another neonatal facility within the first 24 h of life. Exclusion from this group will apply in instances where informed consent is not provided, where no serum bile acid measurement is available in the specified time frame or where measured bile acid levels are below 10 µmol/L.

The unexposed group will comprise neonates born at the same institution to mothers without a known history of hepatic disease prior to or during the index pregnancy. Controls will be matched according to gestational age at birth, birthweight and sex. Consistent with the ICP-exposed group, informed consent must be obtained a few hours before delivery. Maternal administration of ursodeoxycholic acid at any point during pregnancy, regardless of dosage or timing, will constitute an exclusion criterion for this group, as it may suggest subclinical hepatic dysfunction.

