### Data collection and management

2.7

Data will be prospectively collected using standardized forms specifically developed for the CHOLE-RESP study. Maternal variables will include demographic characteristics (age and body mass index at delivery), obstetric history, biochemical parameters (serum bile acid concentrations, transaminase levels), and pregnancy-related complications (gestational diabetes mellitus, hypertensive disorders, risk of maternal-fetal infection). Information regarding mode of delivery, use of ursodeoxycholic acid therapy and relevant perinatal events (e.g., meconium-stained amniotic fluid) will also be recorded. Neonatal data will include sex, birthweight, gestational age at delivery, Apgar scores at 1, 5, and 10 min, need for resuscitation, diagnosis of RDS and indicators of respiratory morbidity such as surfactant administration, timing and dosing of surfactant therapy, need for mechanical ventilation or non-invasive respiratory support, oxygen supplementation (FiO₂ requirements), severe respiratory complications including pneumothorax, pulmonary hemorrhage and persistent pulmonary hypertension, NICU admission, duration of hospitalization and neonatal mortality.

Each participant will be assigned a unique anonymized code (as previously described), which will be applied to all clinical records and biological samples. The correspondence between personal identifiers and study codes will be stored separately in a password-protected file accessible exclusively to the principal investigator. Data will be entered into a secure electronic database, with regular cross-verification against source documents to ensure data integrity. Laboratory personnel performing biomarker analyses will remain blinded to group assignment. All data collection and management procedures will comply with institutional ethical guidelines and data protection regulations.

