Several design features strengthen the internal validity and feasibility of this study. By including both term and preterm neonates, the study captures the full clinical spectrum of ICP-related deliveries and enables stratified analyses. Also, given the multifactorial nature of neonatal respiratory distress syndrome, statistical models incorporate established clinical risk factors, including gestational age, sex and perinatal infection, to minimize residual confounding and avoid overestimation of the effect of bile acid exposure. Biological samples are collected at defined time points and handled according to standardized protocols, with laboratory personnel blinded to group allocation. The decision to integrate all sampling into clinically indicated procedures minimizes patient risk and reinforces ethical compliance.

Additionally, preliminary retrospective data from our center (June 2020 to December 2024) identified 66 preterm infants born to mothers with ICP among 1,078 preterm births. Although the overall incidence of RDS was not consistently increased, these neonates demonstrated greater respiratory morbidity, with higher requirements for invasive ventilation, non-invasive CPAP and surfactant, as well as longer duration of respiratory support compared with controls. It should be noted that the relatively low number of ICP cases observed retrospectively reflects previous limitations in clinical practice, as bile acid testing was not routinely performed in Romania and often not covered by the public health system. Since October 2024, however, systematic testing for symptomatic mothers and updated obstetric management have been implemented in our institution, already resulting in 54 ICP-exposed neonates recruited within 14 months of prospective enrollment, confirming the feasibility of the study, with control recruitment scheduled to begin after one year. Technical validation of the ELISA kits has been performed in advance and preliminary biomarker analysis will commence once 60 participants are enrolled, with interim results expected to be presented at an international neonatology conference.

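### Exposure is verified by bile acid measurement in the exposed group only, so unrecognised cholestasis can enter the control group and modestly dilute the comparison

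*Protocol article*

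**What the plan says.** Section 2.4 (Eligibility criteria) sets different standards of proof for the two groups.

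- **Exposed group.** Cholestasis is "defined by serum bile acid concentrations exceeding 10 µmol/L within seven days prior to delivery". A neonate is excluded from this group "where no serum bile acid measurement is available in the specified time frame or where measured bile acid levels are below 10 µmol/L".
- **Control group.** Controls are "neonates born at the same institution to mothers without a known history of hepatic disease prior to or during the index pregnancy". Maternal ursodeoxycholic acid at any time in the pregnancy "will constitute an exclusion criterion for this group, as it may suggest subclinical hepatic dysfunction". The section states no bile acid measurement, upper limit or symptom criterion for controls.

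Two other places bear on the point. The Discussion (section 3) reports that, since October 2024, "systematic testing for symptomatic mothers and updated obstetric management have been implemented in our institution", and that control recruitment was planned to start a year into the study. Section 2.7 (Data collection and management) lists among the maternal variables "biochemical parameters (serum bile acid concentrations, transaminase levels". It does not say that these are obtained for every control mother, and it attaches no eligibility rule to them.

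**The concern.** Exposure is measured in one group and presumed absent in the other. The control criterion depends on what is *known*, and what is known depends on who was tested. The ursodeoxycholic acid exclusion shows that the authors recognise hidden liver dysfunction among controls, but it removes only mothers who were treated. A mother who was neither tested nor treated passes.

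Any truly exposed neonates among the controls pull the control results toward those of the exposed group. The differences in respiratory distress syndrome (RDS), surfactant use and biomarkers are then attenuated. The bias runs against the study's directional hypothesis, so it would not produce a false positive. What is at stake is some loss of power and the reading of a null or weak result, since nothing in section 2.4 requires the data that would show how many controls were misclassified.

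Matching on gestational age may add to this. The Introduction associates cholestasis with preterm birth, so controls matched to preterm cases come from births among which cholestasis may be more common.

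**Working it through.** **Inputs**

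- Section 2.3: one-sided independent-samples t-test, effect size 0.5, alpha 0.05, 66 exposed and 132 unexposed, stated power 0.952.
- Introduction: cholestasis "with a reported incidence of 2.9%, depending on geographic and ethnic factors".
- Discussion: 66 of 1,078 preterm births at the site, 66/1,078 = 6.1%.
- Assumed: c, the share of controls who are truly exposed. The documents do not give it. The 2.9% and 6.1% figures serve as scenarios only, because they count all reported or identified cases and not the undiagnosed remainder among eligible controls.

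**Step 1: reproduce the plan's figure.** The noncentrality parameter is d × √(n₁n₂/(n₁ + n₂)) = 0.5 × √(66 × 132/198) = 0.5 × √44 = 3.317, on 196 degrees of freedom. The noncentral t distribution gives one-sided power 0.9516, which agrees with the stated 0.952. With 65 exposed and 130 unexposed the power is 0.949, so 66 is the smallest exposed group that reaches 0.95. The sample size arithmetic is correct and has almost no slack.

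**Step 2: dilute the effect.** If a share c of controls has the exposed-group mean, the expected standardised difference is 0.5 × (1 − c).

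| c (assumed) | Controls affected, of 132 | d | Power at 66/132 | Size needed for 0.95 |
|---|---|---|---|---|
| 0 | 0 | 0.500 | 0.952 | 66/132 |
| 1% | 1.3 | 0.495 | 0.948 | 67/134 |
| 2.9% | 3.8 | 0.486 | 0.941 | 70/140 |
| 6.1% | 8.1 | 0.470 | 0.928 | 75/150 |

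**Step 3: check the spread.** A mixed control group has slightly larger variance, 1 + c(1 − c) × 0.25. Allowing for this, power is 0.940 at 2.9% and 0.926 at 6.1%, so the picture does not change.

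**Step 4: binary outcomes.** If the true risks are r₁ (exposed) and r₀ (unexposed), the observed control risk is (1 − c)r₀ + c·r₁. The observed risk difference is then (1 − c)(r₁ − r₀), so RDS and surfactant differences shrink by the same factor. The article gives no expected risks, so no power is computed for them.

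**The case against.** The strongest reply is that the site's own practice closes most of the route. Symptomatic mothers have been tested systematically since October 2024, control recruitment was to begin about a year later, and controls must be born at the same institution. A mother with pruritus should therefore be tested. If the result is positive, her disease is known and she is already excluded. The under-testing described in the Discussion concerns the retrospective series and not these controls. This stands, and it narrows the concern to asymptomatic cases and to lapses in testing. It does not remove the concern, because eligibility does not depend on the testing having been done.

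A second reply is that the scenarios are generous. Taking 2.9% treats the whole reported incidence as undiagnosed, the 6.1% were identified cases, and milder unrecognised cases would dilute less than the model assumes. This also stands.

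A third is that an article condenses the full protocol, and how a history is checked at screening may be set out there. That is fair for the procedure. However, section 2.4 does give criteria for both groups and makes measurement a condition for one only.

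A reader might infer heavy contamination. At 10% the power would be 0.908 and at 20% it would be 0.841, but nothing in the documents supports shares of that order. A reader might also infer that untested mothers with pruritus are the main source, which the testing policy contradicts.

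**Conclusion.** The asymmetry is real and lies in the eligibility text: mothers with unrecognised or untested cholestasis can supply controls, and the effect is attenuation toward zero. The size is probably modest. Under the two scenarios tied to figures in the article, the effect size falls by 2.9% to 6.1% and power by about 1 to 2.5 percentage points, staying above 0.92. This assumes that misclassified controls have the full exposed-group mean and that the assumed shares are not exceeded. The true share is not given.

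A reader might conclude that a null result would be uninterpretable, or that the sample size is wrong. Neither follows. Attenuation of this order qualifies a null result without emptying it, and the stated calculation reproduces. Nor is the share wholly beyond assessment: bile acids and transaminases are listed maternal variables, so a partial check is possible wherever they were recorded for controls. The point merits a change because the change is cheap and most controls are probably still to be enrolled.

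**What to change.** 1. In section 2.4, add two control exclusions: any recorded bile acid value of 10 µmol/L or more in the index pregnancy; and pruritus in the index pregnancy without a bile acid result below 10 µmol/L in the same seven-day window as for the exposed group. The first makes explicit what the existing history criterion largely implies. The second makes eligibility depend on the site's testing practice having been followed.
2. Prespecify a sensitivity analysis that drops controls whose mothers had raised transaminases without another documented cause.
3. Prespecify a second analysis restricted to controls with a recorded bile acid value below 10 µmol/L, where enough exist.
4. Report the share of controls with a measured bile acid value.
5. State as a limitation on reading a null result that asymptomatic, untested controls remain. The exclusions above do not reach them.

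**Cost.** No new laboratory test is needed. Pruritus is not among the variables in section 2.7, so one screening question must be added. A few candidate controls are lost, from the group that is easier to recruit. The analysis restricted by bile acids will be less precise than the main one.

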**Methods:**

This is a prospective cohort study conducted in a level III neonatal unit in Bucharest, Romania. Neonates born to mothers with ICP (serum bile acids ≥10 μmol/L within seven days before delivery) will be enrolled alongside gestational age, sex and birthweight-matched controls. Serum samples will be collected at 24 h, 48–72 h and on day 7 of life. Quantitative ELISA kits will be used to assess serum biomarkers associated with surfactant dysfunction and lung injury. Perinatal and clinical outcomes will be recorded systematically.

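### Other maternal liver disease is excluded in the control group only, so the stated criteria can count it as ICP exposure

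*Protocol article*

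**What the plan says.** All of the criteria stand in section 2.4 (Eligibility criteria) of the protocol article.

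- **Exposed group, inclusion.** The mother has "a recent diagnosis of intrahepatic cholestasis of pregnancy, defined by serum bile acid concentrations exceeding 10 µmol/L within seven days prior to delivery". The abstract gives essentially the same definition: "Neonates born to mothers with ICP (serum bile acids ≥10 μmol/L within seven days before delivery".
- **Exposed group, exclusions.** Three are listed: no consent, and the two bile acid conditions, "where no serum bile acid measurement is available in the specified time frame or where measured bile acid levels are below 10 µmol/L". Hepatic disease other than ICP is not among them.
- **Unexposed group.** Infants are born "to mothers without a known history of hepatic disease prior to or during the index pregnancy". Any maternal ursodeoxycholic acid during pregnancy also "will constitute an exclusion criterion for this group, as it may suggest subclinical hepatic dysfunction".

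The Introduction describes the condition more narrowly than the criteria do: "ICP is characterized by maternal pruritus and elevated serum bile acid concentrations". It also calls ICP unique to pregnancy. Neither feature is made an entry condition.

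**The concern.** The stated objective is to compare ICP-exposed with unexposed neonates. That comparison is clean only if the groups differ in ICP and not also in how the mothers were screened for other liver disease.

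Here the screen is one-sided. The reason given for the ursodeoxycholic acid exclusion shows that even subclinical hepatic dysfunction was thought worth keeping out of the controls. Nothing equivalent is stated for the exposed group. If some exposed mothers have another liver disease, a difference in RDS, surfactant use or biomarkers mixes the effect of ICP with the effect of that disease. A null or weakened result is open to the same doubt.

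**Working it through.** **Step 1. The rules side by side.** Take one mother with a known liver disease other than ICP.

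| Her bile acids in the last seven days | Exposed group as written | Control group as written |
|---|---|---|
| 12 µmol/L (illustrative) | meets the defining threshold; no listed exclusion applies | barred (known hepatic disease) |
| normal | excluded (below 10) | barred (known hepatic disease) |

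She can enter the study only as ICP-exposed.

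**Step 2. Does anything else in the plan correct for this?**

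- Matching (2.4) covers gestational age, birthweight and sex.
- The covariate named in 2.8 is gestational age.
- The Discussion adds sex and perinatal infection.
- Section 2.7 records obstetric history, transaminases, bile acids and pregnancy complications, but no rule uses them to identify, exclude or adjust for another liver diagnosis.
- The sample codes in 2.6 contrast mothers with cholestasis against mothers without liver disease, which is the same asymmetry.

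**Step 3. The plan's own figure.** The sample size is 66 exposed and 132 unexposed (one-sided t-test, d = 0.5, α = 0.05), with stated power 0.952. The exact noncentral-t calculation gives 0.9516 at 66/132 and 0.9490 at 65/130. The figure reproduces and is not in dispute.

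**Step 4. Possible size.** The documents give no share *f* of exposed mothers with another liver disease, so every input on *f* and its effect below is an assumption.

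*(a) The other disease harms the infant and ICP has no effect.* Assume RDS of 20% otherwise and 40% in these infants. Exposed risk = (1 − f) × 20% + f × 40%.

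- f = 5% (66 × 0.05 = 3.3 infants): 21%, risk ratio 21/20 = 1.05
- f = 15% (66 × 0.15 = 9.9 infants): 23%, risk ratio 23/20 = 1.15

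The standard error of the risk difference at 20% is √[0.20 × 0.80 × (1/66 + 1/132)] = 0.060. The bias is therefore 0.01/0.060 ≈ 0.2 to 0.03/0.060 = 0.5 standard errors, away from the null.

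*(b) The infants concerned carry no ICP effect.* The biomarker shift becomes 0.5 × (1 − f), with SD unchanged.

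| f | Shift | Power at 66/132 |
|---|---|---|
| 0 | 0.500 | 0.952 |
| 5% | 0.475 | 0.933 |
| 10% | 0.450 | 0.908 |
| 15% | 0.425 | 0.878 |

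Here the bias is towards the null. The two scenarios point in opposite directions, and the documents do not say which is closer to the truth.

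**Step 5. Cost of excluding.** If the infants concerned leave and are not replaced, 63, 59 and 56 exposed infants remain at f = 5%, 10% and 15%. Power at d = 0.5 against 132 controls is then 0.946, 0.938 and 0.930. The Discussion reports 54 exposed infants in 14 months, or 54/14 ≈ 3.9 a month. Replacing 10 would take 10/3.9 ≈ 2.6 months, and recruitment is planned to the end of 2027.

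**The case against.** The strongest reply is that the criterion asks for a recent diagnosis of ICP, not merely a laboratory value, and that an obstetric diagnosis implies other causes were considered. The Discussion supports this in part: "systematic testing for symptomatic mothers and updated obstetric management have been implemented in our institution". A reader might infer from the bare threshold that any mother with bile acids above 10 µmol/L qualifies. The documents do not support that reading: the word diagnosis is there, and testing follows symptoms. Even so, the text then says what defines the diagnosis, and that is the threshold alone. Symptom-led testing is hospital practice, not an eligibility rule, and it is not stated for infants transferred in from other facilities, whom 2.4 admits to the exposed group. The reply limits how many such mothers are likely, but does not close the gap.

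Second, the asymmetry has a purpose. Controls need no bile acid measurement, so hepatic history and ursodeoxycholic acid use stand in for proof of non-exposure. The article also often frames the harmful agent as bile acids, whatever their source. Both points are fair. They explain the control criterion, but they do not remove confounding by the other disease itself, and the objectives are worded in terms of ICP.

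Third, a reader might infer that the exposed group is also enriched with hypertensive disease. The documents do not support that. Hypertensive disorders are not excluded from the controls and are recorded as maternal variables under 2.7. At most, hypertensive disease with recognised liver involvement is treated unequally.

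Fourth, a condensed article may leave the work-up for other causes to the full protocol. That would answer a missing detail. Here the article states both sets of criteria, and they differ.

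Finally, the sizes above rest on assumed inputs. Matching and gestational-age adjustment would absorb any part of the effect that runs through prematurity or growth. This stands.

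**Conclusion.** The point holds as a stated asymmetry in eligibility. Known liver disease bars a mother from the control group but not from the exposed group, and neither matching nor any named covariate compensates.

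How many mothers are affected, and the size and direction of any bias, cannot be known from the documents. Symptom-led testing probably keeps the number small. Under the assumed 5–15% share and the assumed doubling of RDS risk, the bias is 1–3 percentage points; under dilution, biomarker power falls from 0.952 to between 0.933 and 0.878. It would be wrong to conclude that the exposed group is materially contaminated, or that a positive result would be spurious. The supported conclusion is narrower: as written, the criteria do not let a difference, or its absence, be attributed cleanly to ICP. This should be corrected because correction is cheap; it does not invalidate the design.

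**What to change.** 1. Add to the exposed criteria in 2.4: no known non-ICP hepatic disease before pregnancy, and no other identified hepatic cause of raised bile acids in the index pregnancy. State that ICP in an earlier pregnancy is not an exclusion; otherwise a literal reading of prior hepatic disease would remove genuine cases.
2. Classify the exposed infants already enrolled (54 at the time of writing) against this criterion, using maternal baseline records only and without reference to neonatal outcomes. Do this before any biomarker result is available; the Discussion plans a preliminary biomarker analysis at 60 participants.
3. Make the primary comparison in infants who meet the common criterion. Report the comparison with all enrolled exposed infants as a sensitivity analysis.

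The cost is one sentence in the criteria and a chart check, which is needed because 2.7 does not name prior hepatic history as a form item. A few exposed infants may leave the primary comparison. At the reported recruitment rate they can be replaced well within the planned period.
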